## Abstract

**Background:**

Rectovaginal fistula (RVF) is an abnormal channel formed by epithelial tissue between the anterior wall of the rectum and the posterior wall of the vagina, which manifests as vaginal gassing and defecation. It is one of the common complications of female pelvic surgeries. With the increased number of proctectomies for rectal cancer, the number of postoperative rectovaginal fistulas also increases. Once RVF occurs, the failure rate is still high with various treatments available. RVF causes great suffering to women and is still a major problem in treatment. Therefore, it is significant for female rectal cancer patients to prevent RVF after rectal cancer surgery. In this study, we introduce a new method to prevent RVF during rectal cancer radical operation.

**Methods:**

In this randomized controlled trial (RCT), all operations are performed according to the principle of total mesorectal excision (TME) radical resection in rectal cancer surgery. All eligible participants will be divided into two groups: the experimental group and the control group. Experimental group: the anterior rectal wall of about 1 cm distal to the anastomosis was dislocated. Before the anastomosis of the rectal end, a fat flap (usually left side) containing the ovarian vascular pedicle was dislocated, measured by 10–15 cm in length and 2 cm in width. The fat flap containing the ovarian vascular pedicle was packed and fixed anterior to the anastomotic stoma with fibrin glue. Control group: surgery will be carried out in accordance with the TME principle. Participants will be compared on several variables, including the incidence of RVF after operation (primary outcomes), the occurrence time of postoperative RVF, the occurrence time of RVF after stoma closure, and other postoperative complications, such as anastomotic leakage, chylous leakage, and intestinal obstruction (secondary outcomes). The follow-up data collection will be conducted according to the follow-up time point, and the baseline data will also be collected for follow-up analysis. By comparing the incidence of rectovaginal leakage between the experimental group and the control group, we aim to explore the feasibility of this method for the prevention of postoperative RVF.

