### Objectives {7}

In this study, packing the anastomotic stoma with a laparoscopic dislocated fat flap containing ovarian vascular pedicle anterior to the anastomosis to explore whether a statistically significant difference in the incidence of rectovaginal leakage between the experimental group and the control group. Thus, we study the feasibility of this method for the prevention of postoperative rectovaginal fistula, and to provide effective clinical evidence for the prevention of postoperative RVF. The purpose study’s main aim is to evaluate the intervention’s efficacy while analyzing feasibility. The purpose of the study is to evaluate the effectiveness of the intervention methods (preventing rectovaginal fistula) in the experimental group, as well as the feasibility of their clinical implementation and promotion. Finally, we attempt to analyze the population suitable for using this method from the final statistical data.

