### Trial design {8}

This is a single-site parallel group RCT designed to explore the feasibility of packing with laparoscopic dislocated fat flap containing ovarian vascular pedicle anterior to the anastomotic stoma after rectal cancer surgery to prevent RVF. It will be implemented in Fujian Medical University Union Hospital from April 2020 to March 2023. Female patients with low and medium rectal cancer who are eligible will be randomly assigned to the experimental group or the control group in a 1:1 allocation ratio. The sample size should achieve the goal of non-inferiority. All patients will sign the informed consent form before they are enrolled in the trial (Additional file 1).

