### Criteria for discontinuing or modifying allocated interventions {11b}

The patient has complications before surgery.The patient agrees to the study but refuses to be randomly assigned.Conditions not suitable for the protocol are found during surgery. For example, during the surgical process, it is found that the patient does not have a suitable free fat flap with ovarian vascular pedicle available, or there is a need to change the surgical method or expand the surgical scope in crisis situations such as bleeding during the operation, or special circumstances with the location, size, and surrounding tissues discovered during the operation.The patient asks to be withdrawn from the protocol.The patient would be unable to continue the protocol due to other postoperative complications.Patients lost to follow-up.

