### Relevant concomitant care permitted or prohibited during the trial {11d}

The similar type of surgery is prohibited during the trialOther complications arising from the procedure can be managed during the trial.Patients who drop out of the experiment during the course of the study will be no longer included in the analyses.Patients with other fatal complications will be no longer included in the analyses.All routine treatment procedures for women in care for low and medium rectal cancer, as deemed appropriate by the patient’s treating clinicians, will be permitted during the trial.Additional clinical review, further treatments, including treatment of rectovaginal fistula, and concomitant medications will be determined by clinical need and will be recorded in follow-up case report forms.

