In the treatment of RVF, scholars [5, 6] had tried trancanal pulling out of the colon combined with greater omentum with pedicle packing and made a success. These results suggest that greater omentum with vascular pedicles may be effective in repairing the posterior vaginal wall injury and strengthening the posterior vaginal wall and anterior rectal wall. Therefore, inspired by this, two domestic studies [7, 8] have achieved good results on the prevention of RVF after rectal cancer by packing the rectovaginal area with greater omentum. However, these two studies have shortcomings. First, the study only investigated the risk of RVF and other complications, and its results did not fully reflect the recovery of the posterior vaginal wall. Second, limited patients were included in these two studies, which were 58 cases in one study [7] and 46 cases in the other [8]. Third, this study showed that the operation time of the experimental group (greater omentum packing group) was significantly longer than that of the control group, and it was statistically significant [7]. In addition, in our actual practice, only a partial of the patient’s omentum was able to be pulled downwards to the space between the rectum and vagina. The uncertainty of preventive effect was increased.

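### Feasibility of implementing the flap is an aim, but no outcome measures it, and the exclusion rules hide women in whom the flap could not be used

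*Protocol article*

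**What the plan says.** - **Aim.** Objectives {7} ranks the aims: evaluate "efficacy while analyzing feasibility". It then adds that the study evaluates effectiveness "as well as the feasibility of their clinical implementation and promotion". Trial design {8} describes the trial as "designed to explore the feasibility of packing with laparoscopic dislocated fat flap containing ovarian vascular pedicle".
- **How feasibility is to be judged.** Abstract, Methods: "By comparing the incidence of rectovaginal leakage between the experimental group and the control group, we aim to explore the feasibility of this method". Objectives {7} takes the same step, going from the difference in RVF incidence straight to feasibility.
- **Outcomes.** The primary outcome is RVF incidence. Secondary outcomes are the timing of RVF, complications, serology, operation duration, quality of life and vaginal discharge. Table 1 has the same list. None concerns obtaining or placing the flap.
- **What the technique requires.** Intervention description {11a} sets the flap's dimensions, the position it must reach and its fixation with fibrin glue. Its length is measured during the operation.
- **What happens when it cannot be done.** Criteria for discontinuing or modifying allocated interventions {11b} includes the case where "it is found that the patient does not have a suitable free fat flap with ovarian vascular pedicle available".
- **Who is analysed.** Concomitant care {11d}: "Patients who drop out of the experiment during the course of the study will be no longer included in the analyses". Statistical methods {20a} leaves out the data of patients who fall away, and {20c} restricts the analysis to complete cases.

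**The concern.** Implementation feasibility and efficacy are different questions. The first asks in what share of women offered the operation the flap can be raised, brought to the required position and fixed. The second asks whether RVF becomes less frequent, or no more frequent, in the group assigned to it. Even an unbiased RVF comparison does not answer the first.

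The plan names no measure for the first question, and its exclusions remove the women who would supply the evidence against the technique. A flap that proves unusable in a substantial minority would look, in the analysed set, like one that always works. Objectives {7} also hopes to identify the population suited to the method. That cannot be done well once the women found unsuitable have been removed.

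**Working it through.** **1. Does any outcome measure technical success?** Requirements in {11a} against Outcomes {12} and Table 1:

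| Requirement | Matching outcome |
|---|---|
| Flap of the stated size raised | None |
| Flap reaches the stated position | None |
| Flap fixed | None |

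Operation duration is the closest item, and it does not show whether the flap was completed.

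**2. Where does a woman without a usable flap go?** Randomisation follows recruitment ({16a}), and the surgeon opens the envelope to carry out the assigned operation ({16c}). The lack of a flap is found during surgery, so after randomisation. She then meets the {11b} criterion. That section covers modifying as well as discontinuing and does not itself say she is excluded. Exclusion follows from joining it to {11d}, {20a} and {20c}. No section says she is kept. For this particular reason, only Group A can lose women.

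**3. Size of the experimental arm.** The plan's figure reproduces: 115 / (1 − 0.20) = 143.75, rounded up to 144. Since 115 is stated per group, the arithmetic points to 144 per group, but the text does not say whether 144 is per group or total. At 1:1 allocation Group A is therefore 144, or 72 if 144 is the total.

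**4. What a count over all allocated women would show.** The documents give no failure rate, so f = 0 to 20% is assumed. With k = N × f rounded and x = N − k successes, success is x / N. The exact (Clopper-Pearson) limits are the 0.025 quantile of Beta(x, N − x + 1) and the 0.975 quantile of Beta(x + 1, N − x). The upper limit is 100% when x = N.

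| N | f | k | Success (exact 95% CI) |
|---|---|---|---|
| 72 | 0% | 0 | 100% (95.0–100) |
| 72 | 5% | 4 | 94.4% (86.4–98.5) |
| 72 | 10% | 7 | 90.3% (81.0–96.0) |
| 72 | 20% | 14 | 80.6% (69.5–88.9) |
| 144 | 5% | 7 | 95.1% (90.2–98.0) |
| 144 | 10% | 14 | 90.3% (84.2–94.6) |
| 144 | 20% | 29 | 79.9% (72.4–86.1) |

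If these failures are excluded as in step 2, the analysed set contains x of x = 100% in every row. It cannot distinguish the rows.

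**5. Can the RVF comparison come out unfavourable?** Inputs from Sample size {14}: 115 per arm, control rate 9.9%, margin 15% (taken as percentage points). The two-sided 95% interval in {20a} corresponds to one-sided 0.025. For a true experimental rate p, the chance of meeting the margin is Φ[(0.15 − (p − 0.099)) / SE − 1.96], where SE = √[(0.099 × 0.901 + p(1 − p)) / 115].

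At p = 0.20, SE = √[(0.0892 + 0.16) / 115] = 0.0466, and Φ(0.049 / 0.0466 − 1.96) = 18%. The same formula gives 97% at p = 9.9%, 63% at 15%, 2.5% at 24.9% and 0.2% at 30%. So this endpoint can fail, but for reasons of efficacy, not because the flap could not be made.

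**The case against.** **Feasibility is used loosely.** The sentences in the Abstract and Trial design {8} go on to speak of preventing RVF, so the word there can mean whether the method prevents fistula, which an RVF comparison does address. This stands for those sections. It does not cover the clause in Objectives {7} on clinical implementation, which has a separate meaning and no measure.

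**Exclusion is an inference.** {11b} allows modification, and a woman who has the standard operation with full follow-up might stay in the analysis. That is fair. On that reading her RVF result is kept, but still no outcome records that the flap failed.

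**The information may exist.** Reasons for discontinuation are monitored ({18b}), flap length is measured ({11a}), and the case report forms are not shown. A count might therefore be recoverable, and it would be wrong to say that failures could never be reported. But monitoring retention gives no definition, no denominator and no commitment to report.

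**Stronger readings that a reader might infer, and that the documents do not support:**
- *Only success is possible.* The RVF comparison can fail (step 5 of the working). Complications and operation time are also compared, and the interim analysis {21b} can lead to discontinuation.
- *The trial would test, or ought to test, an advantage over omentum.* The Discussion says of omentum that "only a partial of the patient’s omentum was able to be pulled downwards to the space between the rectum and vagina", but there is no omentum arm. A success proportion in Group A would not supply that comparison.
- *The 39 earlier cases in the Discussion bound the failure rate.* They are packings already performed, so women without a usable flap need not be among them.

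**Conclusion.** The concern holds in this limited form. One stated aim, the feasibility of clinically implementing the flap, has no matching outcome. RVF incidence is offered in its place, and the {11b} criterion read with {11d}, {20a} and {20c} takes technical failures out of the analysed set. The size is unknown because no failure rate is given. At an assumed 10%, about 7 of 72 or 14 of 144 women allocated to Group A would be affected.

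The complete masking of failures rests on reading those sections together. The lack of an outcome does not. Efficacy is the declared main aim, so this is a gap in a secondary aim. It should be corrected, but it does not of itself undermine the main comparison.

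**What to change.** - Add a secondary feasibility outcome: the proportion of all women allocated to Group A in whom the flap was raised, placed and fixed as {11a} describes, with an exact 95% confidence interval and the reason for each failure.
- State that a woman with no suitable flap under {11b} counts as a failure on this outcome, and keep her in follow-up and in the Group A denominator. Align {11d}, {20a} and {20c} with this.
- Present RVF incidence as the efficacy outcome, and no longer as evidence of implementation feasibility, in the Abstract and Objectives {7}.

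The cost is wording plus one yes/no field with a reason on the operative case report form; flap length is already measured. The reported success rate will probably fall below 100%. Trial status reports 96 women recruited, with recruitment continuing, so the item can be collected prospectively for the rest. For women already operated on it may be recoverable from operative notes, which the protocol does not confirm.

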**Discussion:**

This RCT will explore the feasibility of packing with a laparoscopic dislocated fat flap containing an ovarian vascular pedicle anterior to the anastomotic stoma after rectal cancer surgery to prevent RVF.

**Trial registration:**

Chinese Clinical Trial Registry (ChiCTR) registration ChiCTR2000031449. Registered on June 26, 2019. All items of the WHO Trial registration data set can be found within the protocol.

**Supplementary Information:**

The online version contains supplementary material available at 10.1186/s13063-023-07721-2.

## Introduction

### Background and rationale {6a}

Rectovaginal fistula (RVF) is an abnormal channel formed by epithelial tissue between the anterior wall of the rectum and the posterior wall of the vagina, which manifests as vaginal gassing and defecation. It is one of the common complications of female pelvic surgeries. With the increased number of proctectomies for rectal cancer, the number of postoperative RVF also increases with the incidence reported to be 0.9–9.9% in most literatures [1, 2]. Once RVF occurs, the failure rate is still high with various treatments available [3]. Most of the existing studies focus on the treatment instead of prevention for RVF. Recent researches on postoperative RVF of low-middle rectal cancer have reported that intraoperative measures can effectively reduce the incidence of RVF in terms of surgical techniques [4], such as pushing and pulling the uterine and vaginal walls upward and outward which can make a certain tension with the anterior rectal wall; control the frequency of electric knife or ultrasonic knife; examining the vaginal wall via pelvis and vagina prior anastomat triggering to avoid being clamped; and blocking the vaginal wall with pressure intestinal spatula.

Researchers [5, 6] had tried to trancanal pulling out of the colon combined with greater omentum with pedicle packing and made a success in the treatment of RVF. These results indicated that greater omentum with vascular pedicles could be effective in repairing the posterior vaginal wall injury and strengthening the posterior vaginal wall and anterior rectal wall. Next, two domestic studies [7, 8] reported to make a success on the prevention of RVF by packing the rectovaginal area with greater omentum. But in our actual practice, the greater omentum could be pulled down to the space between the rectum and vagina in some patients, which made the uncertainty of the prevention effect increase.

Inspired by preventing RVF through packing the rectum and vagina with vascular pedicled greater omentum with its shortcomings, we propose the prevention of RVF by using autologous fat flap containing ovarian vascular pedicle to pack the rectum and vagina after radiotherapy and chemotherapy in female rectal cancer patients.RVF causes great suffering to women and is still a major problem in treatment. Therefore, a new method with good effect in preventing RVF during rectal cancer radical operation is needed and to be validated by a high-quality randomized controlled trial (RCT).

### Objectives {7}

In this study, packing the anastomotic stoma with a laparoscopic dislocated fat flap containing ovarian vascular pedicle anterior to the anastomosis to explore whether a statistically significant difference in the incidence of rectovaginal leakage between the experimental group and the control group. Thus, we study the feasibility of this method for the prevention of postoperative rectovaginal fistula, and to provide effective clinical evidence for the prevention of postoperative RVF. The purpose study’s main aim is to evaluate the intervention’s efficacy while analyzing feasibility. The purpose of the study is to evaluate the effectiveness of the intervention methods (preventing rectovaginal fistula) in the experimental group, as well as the feasibility of their clinical implementation and promotion. Finally, we attempt to analyze the population suitable for using this method from the final statistical data.

### Trial design {8}

This is a single-site parallel group RCT designed to explore the feasibility of packing with laparoscopic dislocated fat flap containing ovarian vascular pedicle anterior to the anastomotic stoma after rectal cancer surgery to prevent RVF. It will be implemented in Fujian Medical University Union Hospital from April 2020 to March 2023. Female patients with low and medium rectal cancer who are eligible will be randomly assigned to the experimental group or the control group in a 1:1 allocation ratio. The sample size should achieve the goal of non-inferiority. All patients will sign the informed consent form before they are enrolled in the trial (Additional file 1).

## Methods: participants, interventions, and outcomes

### Study setting {9}

All eligible participants will be recruited through the outpatient clinic or inpatient, hospital-based WeChat advertising, and posters in the Fujian Medical University Union Hospital.

### Eligibility criteria {10}

All female patients undergoing low and medium rectal cancer surgery during the study period will be screened for eligibility. All eligible participants undergo a formal informed consent process by the research assistant and a research clinician. The interventions are delivered by the research clinicians.

#### Inclusion criteria

Patients who meet the following conditions will be included:Refer to the diagnostic and classification criteria for colorectal cancer of the American Joint Committee on Cancer (AJCC) and The Union for International Cancer Control (UICC) [9], seventh edition. The diagnosis of rectal cancer is confirmed with cTNM staging, T3–4NxM0.Female patients with ovarian failure after chemoradiotherapy or postmenopausal patients (serum FSH > 40U/L, LH > 20 IU/L, and E2 < 10–20 pg/mL).Received preoperative neoadjuvant chemoradiotherapy: radiotherapy regimen (long-range radiotherapy: DT50Gy/25F), chemotherapy regimen (XELOX regimen).Preoperative tumor distance to anal margin ≤ 7 cm.No other primary malignant tumor has been diagnosed.The clinical data are complete and prophylactic ileostomy is acceptable.The consent is signed.

#### Exclusion criteria

Patients who meet any of the following conditions will be excluded:The history of major abdominal surgery.Emergency surgery (perforation, bleeding, intestinal obstruction, etc.).Patients with severe heart, lung, liver, and kidney diseases who cannot tolerate laparoscopic surgery.Patients with coagulation dysfunction.Patients after hysterectomy and oophorectomy.

### Who will take informed consent? {26a}

After being evaluated according to the inclusion and exclusion criteria, eligible individuals will be approached for participation in the trial by a researcher with a research assistant during their preoperative visit. All participants will be clearly informed about the potential benefits and risks of the trial before they sign the informed consent.

### Additional consent provisions for collection and use of participant data and biological specimens {26b}

Not applicable. There are no plans for secondary or ancillary studies using the data generated in this trial.

## Interventions

### Explanation for the choice of comparators {6b}

This trial will compare the efficacy of preventing RVF. Compared to the control group, the experimental group would add a step to an operation of packing with a dislocated fat flap containing ovarian vascular pedicle anterior. The operations will be performed by the same clinic doctor of the trial at Fujian Medical University Union Hospital. It has the advantages of not being easily perceived by the patient and a higher feasibility of operation.

### Intervention description {11a}

#### Group A (experimental group)

All operations will be performed according to the principle of TME radical resection in rectal cancer surgery. The anterior rectal wall of about 1 cm distal to the anastomosis will be dislocated.Before the rectal anastomosis, the researcher would expose one side of the ureter (usually the left side), dislocate the fat flap containing ovarian vascular pedicle to avoid damage of the ureter, and dissect ovarian vessels proximal to the kidney. After dislocating the fat flap, the size of the packing end would be 2 cm (width) × 4–5 cm (length) at least, with a 10–15 cm in total length, which would be measured by a thread during the operation. This length would ensure to pull-down to 5 cm below the anastomosis (Figs. 1, 2, and 3).After rectal anastomosis, a large amount of normal saline will be used to rinse the pelvic cavity. The liquid will be sucked up. The surface of the rectum and vagina will be dried with gauze.The fat flap containing ovarian vascular pedicle will be flipped downward and packed between the anastomotic stoma and vagina (9 o’clock to 3 o’clock of the outer wall of the rectum in lithotomy position), then fixed with medical fibrin glue. (Fig. 4)

